**Appendix 1:** Trial Registration Summary

| **Data category** | **Information** |
| --- | --- |
| Primary registry and trial identifying number | Australian New Zealand Clinical Trials Registry (ANZCTR)  ACTRN12621001195842 |
| Date of registration in primary registry | 8 September 2021 |
| Secondary identifying numbers | Nil |
| Source(s) of monetary or material support | Insulet Australia Pty Ltd |
| Primary sponsor | St Vincent’s Hospital Melbourne |
| Secondary sponsor(s) | Nil |
| Contact for public queries | *[name], MD*  St Vincent’s Hospital Melbourne, Australia *[name]*  *[contact]* |
| Contact for scientific queries | *[name], MD* St Vincent’s Hospital Melbourne, Australia |
| Public title | Comparison of Treatment Satisfaction between the Omnipod Insulin Pump and Usual Care in Adults with Type 1 Diabetes in Australia |
| Scientific title | A Pilot Study Comparing Treatment Satisfaction with the Omnipod Insulin Pump Compared with Usual Care in Adults with Type 1 Diabetes Living in Australia |
| Countries of recruitment | Australia |
| Health condition(s) or problem(s) studied | Type 1 diabetes |
| Intervention(s) | Active comparator: Omnipod DASH insulin pump for 24 weeks  Placebo comparator: Participants' usual diabetes management (either multiple daily insulin injections or insulin pump therapy) for 12 weeks, followed by 12-weeks of using Omnipod DASH insulin pump (total duration of 24 weeks) |
| Key inclusion and exclusion criteria | Ages eligible for study: 18 to 70 years Sexes eligible for study: both Accepts healthy volunteers: no  Inclusion criteria: clinical diagnosis of type 1 diabetes (as defined by the American Diabetes Association) of at least six months duration managed with multiple daily injections (MDI) or insulin pump therapy (IPT), age 18-70 years old, fluent in English (reading and writing), willing to perform at least four self-monitoring of blood glucose (SMBG) readings each day, willing to learn how to carbohydrate count and to apply this knowledge, HbA_1c_ <10.0%, willing to use an Omnipod DASH insulin pump, has a computer with internet access, has access to a smart device with data plan.  Exclusion criteria: using real time-CGM defined as use >25% of the time during the past 3 months (Abbott Libre allowed), an episode of severe hypoglycemia or diabetic ketoacidosis within the preceding three months, a physical or intellectual disability precluding the use of insulin pump therapy, severe renal impairment (eGFR less than 15 ml per minute per 1.73m^2^), haemoglobinopathy or hemolytic anemia due to its interference with HbA_1c_ assays, major life-threatening illness impacting immediate life expectancy, use of any non-insulin glucose-lowering agent within the past 3 months, oral or injected corticosteroid use within the past 3 months, pregnancy or pregnancy planned within study period, uncontrolled thyroid disease, celiac disease or hypertension, a requirement for more than 200 I.U. of insulin every two days. |
| Study type | Interventional Allocation: randomised Intervention model: other, participants will be randomised to continue their usual care or commence on the Omnipod DASH insulin pump at the start of the intervention (Week 0) for 12 weeks, then both arms will be on the Omnipod DASH insulin pump for another 12 weeks as an extension Masking: open (masking not used) Primary purpose: treatment |
| Date of first enrolment | 15 July 2021 |
| Target sample size | 64 |
| Recruitment status | Recruiting |
| Primary outcome(s) | Treatment satisfaction measured by the difference in the Diabetes Technology Questionnaire (DTQ) score (Week 12 post intervention commencement) |
| Key secondary outcomes | Psychological outcomes measured by the Problem Areas in Diabetes (PAID) questionnaire, Pittsburgh Sleep Quality Index (PSQI), Hypoglycemia Fear Short-Form Survey (HFS-11-SF) and Diabetes Medication System Rating Questionnaire Short-Form (DMSRQ-SF).  Effectiveness, efficiency and user satisfaction with Omnipod DASH insulin pump measured via User Experience Questionnaire (UEQ) and System Usability Scale (SUS).  Acceptability of Omnipod DASH insulin pump device assessed via an open-ended one-on-one interview.  Masked continuous glucose monitor (CGM) metrics including percentage of time in range (3.9-10 mmol/L), percentage of time <3.9 mmol/L, percentage of time >10 mmol/L, percentage of time >13.9 mmol/L, percentage of time <2.8 mmol/L and mean glucose.  HbA_1c_ via blood test.  Number of symptomatic hypoglycemic events defined as an event with typical symptoms of hypoglycemia accompanied by measured plasma glucose concentration of 3.9 mmol/L or less, recorded by KeyLead App.  Length of time to change pods, length of time to change insulin pump sets, number of insulin infusion line occlusions and pod failures.  Healthcare professional perception of Omnipod DASH insulin management system as assessed via an open-ended 30-minute interview. |

**Appendix 2: SVHM HREC Approved Participant Information and Consent Form**

**Appendix 3:** Statistical Analysis Plan

**Statistical Analysis Plan – A Pilot Study Comparing Treatment Satisfaction with the Omnipod^TM^ Insulin Pump Compared with Usual Care in Adults with Type 1 Diabetes Living in Australia.**

**Research Question**

To examine study feasibility and acceptability of Omnipod DASH^®^ System compared with usual care i.e. multiple daily injections (MDI) or conventional insulin pump therapy (IPT) in people living with type 1 diabetes who are monitoring their glucose levels on capillary blood using a glucose meter. Please refer to study protocol where all aspects of the study design are provided.

**Study Cohort**

Sixty-four adults with a diagnosis of type 1 diabetes managed with MDI or IPT will be recruited from four specialist diabetes centres in Victoria, Australia.

**
[figure not shown]
**

**Figure 1:** Overview of study design

**Primary Variables and Outcomes of Interest**

1. Acceptability of Omnipod DASH^®^ System compared with usual care assessed by the difference in Diabetes Technology Questionnaire (DTQ) “current” (DTQ-current) scores between baseline pre-randomisation and 12 weeks after the intervention in those participants completing the protocol via a Qualtrics survey (1, 2)

2. Feasibility of study completion as assessed by the proportion of participants who complete the study per-protocol. This will be defined as at least 0.80.

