**Order of Statistical Analyses**

The exploratory nature of the study **precludes** a power calculation. N=64 participants will provide exploratory data across clinical sites and insulin delivery modalities (MDI and IPT).

The primary analyses will assess differences in the DTQ current score between the

Omnipod group and usual care at baseline and week 12 . This will be done on the basis of intention to treat using analysis of covariance (ANCOVA), with adjustment for baseline patient characteristics. A p-value of <0.05 will be considered statistically significant. Residuals will be explored to assess model fit. If model fit is poor, non-parametric analysis will be performed instead.

Continuous secondary outcomes will be assessed using ANCOVA, count outcomes will be assessed using a Poisson or negative binomial regression model and for binary outcomes, logistic regression models will be fitted.

A subgroup analysis will be conducted by baseline insulin delivery mode at 12 and 24 weeks in the form of an interaction term in the regression model or by stratifying analysis if non-parametric methods are required.

There will be no adjustment for multiple comparisons, all primary, secondary and tertiary outcome results will be reported.

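### The SAP limits the primary DTQ-current outcome to protocol completers but analyses it by intention to treat, without defining completion or saying which population governs

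*Combined protocol and SAP*

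**What the plan says.** In the SAP (Appendix 3), section Primary Variables and Outcomes of Interest, item 1 is the difference in DTQ-current between pre-randomisation baseline and week 12, "in those participants completing the protocol via a Qualtrics survey". Item 2 of the same list is a second primary outcome: "Feasibility of study completion as assessed by the proportion of participants who complete the study per-protocol. This will be defined as at least 0.80".

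The section Order of Statistical Analyses returns to the same score, arms and time points (baseline and week 12) and states: "This will be done on the basis of intention to treat using analysis of covariance (ANCOVA), with adjustment for baseline patient characteristics". It sets a significance threshold of p<0.05 for this analysis.

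The Trial Registration Summary (Appendix 1) gives the week-12 DTQ difference as the primary outcome and names no analysis population. It describes an open-label trial with a 12-week randomised comparison, followed by a 12-week extension in which both arms use Omnipod.

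Three things do not appear in the supplied text:
- a definition of completing the protocol, or its time point;
- a statement that one population is primary and the other supplementary;
- a rule for missing week-12 DTQ scores.

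**The concern.** All randomised participants and protocol completers are different sets, and the SAP attaches both to one primary outcome. Completion is observed only after randomisation, so a completers-only comparison no longer has the protection of randomisation. Here that could matter: participants know their arm, the outcome is how satisfied they are with treatment, and willingness to stay may depend on both.

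The missing definition adds a second problem. If completion means week 24, a participant who gave a valid week-12 score and left during the extension would be dropped from a week-12 comparison because of something that happened after it.

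At stake are the meaning of the primary estimate and its possible bias. No sample-size figure depends on the point, because the SAP says a power calculation is precluded.

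**Working it through.** **Side by side.** Item 1 and the analysis section name the same instrument version (DTQ-current), the same comparison (Omnipod against usual care) and the same times (baseline, week 12). They differ in population. There is no plan figure to reproduce, so the arithmetic below only shows the possible scale.

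**Inputs from the documents.** N = 64; completion criterion at least 0.80; significance level 0.05.

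**Assumptions not in the documents.** 1:1 allocation, so 32 per arm; a two-sided test; all 64 as the denominator for completion; non-completers whose DTQ would differ from that of completers by g = 0.5 to 1.0 SD, equally in both arms.

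**Step 1: how far the two populations can differ with feasibility still met.** 0.80 × 64 = 51.2, so 52 completers are needed. 64 − 52 = 12 non-completers, and 12/64 = 19%. If the criterion is missed, the gap is larger.

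**Step 2: bias of a completers-only comparison.** Within an arm, the completer mean differs from the full-arm mean by (share not completing) × g. The bias of the difference between arms is therefore [(a − b)/32] × g, where a and b are the numbers of non-completers in the two arms.

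| Split of the 12 | (a − b)/32 | g = 0.5 SD | g = 1.0 SD |
| --- | --- | --- | --- |
| 6/6 | 0 | 0 | 0 |
| 9/3 | 0.1875 | 0.09 SD | 0.19 SD |
| 12/0 | 0.375 | 0.19 SD | 0.38 SD |

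The zero for an even split depends on g being equal in the two arms. With g = 1.0 in one arm and 0.5 in the other, a 6/6 split gives (6/32) × (1.0 − 0.5) = 0.09 SD.

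**Step 3: precision.** The 95% CI half-width for the unadjusted difference is 1.96 × √(1/n₁ + 1/n₂):
- 32 and 32: 1.96 × √(2/32) = 0.49 SD
- 26 and 26: 1.96 × √(2/26) = 0.54 SD
- 23 and 29 (9/3 split): 0.55 SD
- 20 and 32 (12/0 split): 0.56 SD

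Losing 12 people widens the interval only modestly. In the uneven splits of the table, the bias runs from about a sixth (0.09/0.55) to about two thirds (0.38/0.56) of the half-width. Selection matters more than precision.

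**The case against.** The best defence is that only the analysis section prescribes an analysis, and it names intention to treat. On that view item 1 merely lists a variable and how it is collected, and its awkward phrase means those who return the survey. The analysis would then be by assigned arm on available scores, with a missing-data gap and no rival population.

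Part of this stands. Intention to treat is prespecified, so a reader might infer that the choice of population has been left open until the data are seen; the documents do not support going that far. The survey-return reading is weaker. Item 2, directly below, speaks of completing the study per protocol, and Secondary Feasibility Endpoints uses the survey phrase for the mode of assessment. Even on that reading, the set depends on a post-randomisation event and missing scores have no stated handling.

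Three further limits are fair:
- **Week 24.** A reader might infer that everyone who leaves during the extension is excluded. That is conditional: the registration summary calls the second 12 weeks an extension, and completion could mean the randomised stage.
- **Unseen text.** The SAP refers to a study protocol for all design aspects, and its body is not in the supplied text. A definition of completion may be there. It would not by itself remove the conflict between two sections of the SAP.
- **Source of the loss.** A reader might charge the whole drop from 64 to 52 to the completer wording. Intention to treat recovers only those who supplied a week-12 score; people who withdrew without one are missing under either population.

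**Conclusion.** The inconsistency is real and needs correcting. As written, item 1 restricts the primary outcome to a set chosen after randomisation, the analysis section does not, and nothing supplied reconciles them. The two sets can differ by up to 12 of 64 participants (19%) with the feasibility criterion still met.

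The bias figures, 0 to 0.38 SD, are illustrations under the stated assumptions. It is tempting to conclude that a completers-only analysis must flatter Omnipod. The documents give no dropout rate by arm and no DTQ data on people who leave, so neither size nor direction is established. If non-completers are the less satisfied, an excess of them in the Omnipod arm favours Omnipod, and an excess in usual care favours usual care.

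Rating: should fix. This is an exploratory pilot whose analysis section already names intention to treat, but it attaches a significance test to this outcome, so the population has to be unambiguous.

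**What to change.** 1. Reword item 1 to: *DTQ-current at week 12 in all randomised participants, analysed in the arm assigned, regardless of device use or later completion.*
2. Use every observed week-12 score, including scores from participants who stopped the device or left later. The supplied text does not say whether people who stop are still sent the survey, so state that they are.
3. Name one method for missing week-12 scores and one simple sensitivity analysis to go with it. Several methods would serve; what matters is that one is fixed in advance.
4. Define completing the protocol, with its time point, for the feasibility outcome in item 2.
5. Label any completer analysis as supplementary.

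The cost is SAP wording and a little extra analysis, with no added participants or visits.

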**Secondary Feasibility Endpoints**

User acceptance assessed via a Qualtrics survey including DTQ-current scores at 24 weeks; and DTQ-change scores at 12 weeks and 24 weeks (1, 2). Composite total scores for both DTQ change and current will be calculated by taking the average of item responses. Cronbach’s alpha reliability coefficient will be calculated for both versions (current and change) of the DTQ.

For process and resource outcomes, we will describe continuous data by summaries (e.g. means, medians, ranges) and categorical variables with frequency distributions. Outcomes, to be collected continuously in real-time using the study’s phone app, Keylead Health^TM^ platform, will include time duration and frequency of education, time to change pods, time to change insulin pump sets, and time to upload devices. Line occlusions (n) recorded by Keylead Health^TM^ platform, calls to help-lines (n), and skin reactions (n). A line occlusion will be predefined as 1) unexplained blood glucose >14mmol/L, not responsive to a corrective dose with at least a 2.8mmol/L drop within one hour, or 2) blood glucose >14mmol/L with ketones ≥ 0.6 mmol/L, or 4) occurrence of a non-resolvable pump occlusion alarm.

**Secondary Scientific Endpoints**

Participant reported endpoints also to be assessed via a Qualtrics survey including the Problem Areas in Diabetes (PAID) (3), Pittsburgh Sleep Quality Index (PSQI) (4), Hypoglycaemia Fear Survey – Short Form (HFS-II-SF) (4) and the Diabetes Medication System Rating Questionnaire – Short Form (DMSRQ-SF) (5).

At week 12 and 24 visits, the 26-item User Experience Questionnaire (UEQ) (6) and 10-item System Usability Scale (SUS) (7) will provide general measures of effectiveness, efficiency and user satisfaction with the Omnipod DASH^®^ insulin pump.

| Outcome - Questionnaire | Method of Scoring |
| --- | --- |
| Diabetes Technology Questionnaire (DTQ) Current Score | Mean of total score (out of 150)  Mean score for each question (out of 5) |
| Diabetes Technology Questionnaire (DTQ) Change score | Mean of total score (out of 150)  Mean score for each question (out of 5) |
| Problem Areas in Diabetes (PAID) | Mean of total score (out of 100) |
| Pittsburgh Sleep Quality Index (PSQI) | Mean of total score (out of 21)  Mean score for each section:   - Sleep quality - Sleep latency - Sleep duration - Habitual sleep efficacy - Sleep disturbance - Use of sleeping medication   Daytime dysfunction |
| Hypoglycaemia Fear Survey (short-form)(3) | Mean of total score (out of 44)  Mean score for each subscale: Behaviour (B), Worry (W) |
| Diabetes Medication System Rating Questionnaire – Short Form | Mean of total score (out of 72)  Mean score for each section:   - Convenience satisfaction - Negative events - Interference - Self-monitoring of blood glucose burden - Efficacy - Social burden - Wellbeing - Treatment satisfaction - Treatment preference |
| User Experience Questionnaire (UEQ) | Mean of each scale:   - Attractiveness - Perspicuity - Efficacy - Dependability - Stimulation - Novelty |
| System Usability Scale (SUS) | Mean of total score (out of 100) |

At the 12 and 24-week post-randomisation visit, participants using Omnipod DASH^®^ will be interviewed about the acceptability of the device and their recommendations for further refinement in implementation of the education. These interviews are expected to take approximately 20 to 30 minutes and will be audio recorded and transcribed for later analysis using Braun and Clarke’s reflexive thematic analysis approach (8).

Health Care Professionals (one from medical and nursing) from each site will be interviewed. These interviews are expected to take approximately 20 to 30 minutes and will be audio recorded and transcribed for later thematic analysis (8).

Glycaemic endpoints measured at the end of each stage will include CGM metrics standardized according to convention as described by Maahs *et al* (9) and HbA1c. Symptomatic hypoglycaemia, recorded on the Keylead Health^TM^ platform, is defined as an event during which typical symptoms of hypoglycaemia are accompanied by a measured plasma glucose concentration ≤70 mg/dl (3.9 mmol/l) and difference in the number hypoglycaemic events between the omnipod and standard care group will be examined.^6^

**Order of Statistical Analyses**

The exploratory nature of the study **precludes** a power calculation. N=64 participants will provide exploratory data across clinical sites and insulin delivery modalities (MDI and IPT).

The primary analyses will assess differences in the DTQ current score between the

Omnipod group and usual care at baseline and week 12 . This will be done on the basis of intention to treat using analysis of covariance (ANCOVA), with adjustment for baseline patient characteristics. A p-value of <0.05 will be considered statistically significant. Residuals will be explored to assess model fit. If model fit is poor, non-parametric analysis will be performed instead.

Continuous secondary outcomes will be assessed using ANCOVA, count outcomes will be assessed using a Poisson or negative binomial regression model and for binary outcomes, logistic regression models will be fitted.

A subgroup analysis will be conducted by baseline insulin delivery mode at 12 and 24 weeks in the form of an interaction term in the regression model or by stratifying analysis if non-parametric methods are required.

There will be no adjustment for multiple comparisons, all primary, secondary and tertiary outcome results will be reported.

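### The primary DTQ comparison is labelled intention to treat, but as written it is a completer analysis, with no step for missing week-12 scores and possible bias in either direction

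*Combined protocol and SAP*

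**What the plan says.** Three places in the SAP (Appendix 3) and one in the registration summary (Appendix 1) bear on this.

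- **SAP, Order of Statistical Analyses.** The primary analysis compares DTQ-current between Omnipod and usual care at week 12: "This will be done on the basis of intention to treat using analysis of covariance (ANCOVA". The model adjusts for participants' characteristics at baseline. Significance is declared at p<0.05. The only fallback is a non-parametric analysis if the model fits poorly.
- **SAP, Primary Variables and Outcomes of Interest, item 1.** The same outcome is defined as assessed "in those participants completing the protocol via a Qualtrics survey".
- **SAP, same section, item 2.** Feasibility is judged by "the proportion of participants who complete the study per-protocol. This will be defined as at least 0.80".
- **Registration summary, Study type.** "Masking: open (masking not used", with 12 randomised weeks followed by 12 weeks on Omnipod in both arms.

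The SAP text contains no imputation, no likelihood model for incomplete data, no missing-data sensitivity analysis and no definition of the intention-to-treat set.

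**The concern.** Intention to treat tells the reader that everyone randomised contributes to the comparison. An ANCOVA of a week-12 score cannot use a participant who has no week-12 score unless a further step is specified, and none is. The outcome definition does not fill the gap: it points to completers.

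The type of outcome makes this matter. The DTQ is a self-report of satisfaction with diabetes technology, answered by online survey by people who know their allocation. The reasons someone stops responding, such as disliking the pod or being disappointed to remain on usual care, may be close to what the questionnaire measures. The difference among responders can then depart from the difference among all randomised participants. The label would not reveal it, and no planned analysis would show how much departure is needed to change the conclusion.

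**Working it through.** **What the plan gives.** The total is 64. No effect size, SD or expected loss is stated ("The exploratory nature of the study precludes a power calculation"), so there is no planned figure to reproduce.

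**Assumptions not in the documents.** 32 per arm; two-sided 5% test; baseline DTQ-current among the ANCOVA covariates, with correlation r = 0.5 to week 12; no true effect in all randomised participants; leavers scoring 0.5 or 1.0 SD below stayers.

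**Step 1: an illustrative number missing.** 51/64 = 0.797 fails the 0.80 criterion and 52/64 = 0.8125 meets it, so a study that just meets it has 12 non-completers (18.75%). I use 12 missing scores only as a convenient scenario. The criterion concerns completing the study per-protocol, not returning the week-12 DTQ.

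**Step 2: bias formula.** If a fraction p of an arm is missing and stayers exceed leavers by a gap g, the stayers' mean exceeds the whole-arm mean by p × g. Hence

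bias = (lost_O/32) × g_O − (lost_U/32) × g_U, where O is Omnipod and U is usual care.

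This holds when the gap is unrelated to baseline. If baseline carries its share, leavers also sit r × g lower at baseline and ANCOVA removes r² × g. The bias is then multiplied by 1 − r² = 0.75.

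**Step 3: precision.** Half-width = t × √[(1 − r²)(1/n₁ + 1/n₂)].

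- 32 and 32: 2.00 × √(0.75 × 2/32) = 2.00 × 0.217 = 0.43 SD
- 26 and 26: 2.01 × √(0.75 × 2/26) = 2.01 × 0.240 = 0.48 SD

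**Step 4: gap in Omnipod leavers only.** Each range runs from g = 0.5 to g = 1.0. The false-positive rate comes from the non-central t distribution with non-centrality bias/SE.

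| Missing O/U | Bias, gap unrelated to baseline | False positives | Bias × 0.75 | False positives |
|---|---|---|---|---|
| 6/6 | +0.09 to +0.19 SD | 7% to 12% | +0.07 to +0.14 SD | 6% to 9% |
| 8/4 | +0.13 to +0.25 SD | 8% to 17% | +0.09 to +0.19 SD | 7% to 12% |
| 10/2 | +0.16 to +0.31 SD | 10% to 24% | +0.12 to +0.23 SD | 8% to 16% |

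For example, 10/2 with g = 1.0 gives 10/32 = 0.3125, and 0.3125 × 0.75 = 0.234.

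**Step 5: other patterns.**

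- 6/6 with the same gap in both arms: 6/32 × g − 6/32 × g = 0, and the error rate stays at 5%.
- 8/4 with the same gap in both arms: 4/32 × g = +0.06 to +0.13 SD, or +0.05 to +0.09 SD after the 0.75 factor.
- 2/10 with the gap in usual care only: −0.16 to −0.31 SD, or −0.12 to −0.23 SD after the 0.75 factor. This is against Omnipod.
- No gap in either arm: no bias.

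**Step 6: simulation check.** ANCOVA was simulated 4,000 times per scenario with r = 0.5 and lower scorers more likely to be lost. Bias was about zero with purely random loss and with the same score-dependent loss in both arms. It was +0.13 SD (9.3% false positives) with 6/6 and score-dependent loss in Omnipod only, +0.29 SD (22%) with all 12 lost from Omnipod, and −0.28 SD (21%) with all 12 lost from usual care.

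**The case against.** The strongest reply is that much of this rests on silence. The SAP nowhere says that participants without a week-12 score are dropped. Its Research Question section refers the reader to the study protocol for design details, and the protocol body is not part of the text reviewed. Follow-up after stopping the assigned treatment could be set out there. That is fair, and limits the claim to what the SAP text does if followed as it stands. It does not dispose of the point: ANCOVA needs an observed or imputed outcome, and item 1 of the outcomes section names completers. If a missing-data rule exists elsewhere, the SAP should cite it.

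A reader might infer that the plan tolerates 20% missing week-12 scores. It does not say so. Someone can leave after week 12, or deviate from the protocol, fail the 0.80 criterion and still have a week-12 DTQ. Equally, nothing in the criterion caps the number of missing scores.

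A reader might also infer that the bias must favour Omnipod. The documents support no direction. Usual-care participants also know their allocation and may leave dissatisfied. The largest figures need a lopsided split, a 1 SD gap, no gap in the other arm and no help from baseline adjustment.

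Finally, this is an exploratory pilot with no power calculation. That lowers the consequence, but the SAP still attaches a significance test to this comparison.

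**Conclusion.** The concern holds in a limited form. The primary comparison is called intention to treat, but the stated method and the outcome definition together give a completer analysis, with no check on what missing scores do to it.

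If 12 of 64 scores were missing and only Omnipod leavers scored 0.5 to 1.0 SD lower, the bias would be about +0.07 to +0.19 SD with even loss. At 10/2 with a 1 SD gap it would reach about +0.23 to +0.31 SD. Against a half-width of about 0.48 SD with 52 scores, that is not negligible. Bias vanishes under equal loss and equal gaps, and reverses if the loss is concentrated in usual care. These figures are conditional on the assumed allocation, correlation, number missing and gaps, and none is a forecast. The documents do not support saying that the plan accepts a 20% loss of primary outcome data, or that the result will overstate satisfaction with the device.

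**What to change.** 1. Reconcile item 1 of Primary Variables and Outcomes of Interest with Order of Statistical Analyses, so that the primary comparison covers all randomised participants, and define that set.
2. Send the week-12 DTQ to every randomised participant who has not withdrawn consent, including those no longer on the assigned treatment, and include these scores in the ANCOVA by allocated arm. If the protocol already provides for this, cite it in the SAP.
3. Prespecify a sensitivity analysis using multiple imputation by arm, with imputed scores shifted in steps from 0.25 to 1.0 SD in each arm separately. Report the shift at which the conclusion changes, and the number of missing scores by arm.

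Multiple imputation need not become the primary analysis. With 64 participants, and with the other questionnaires collected by the same online route and so probably missing together, it would add little to a baseline-adjusted ANCOVA. The gain comes from recovering scores and from the delta shifts.

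The cost is some SAP wording, a little more analysis and continued use of a survey already in place. The sensitivity estimate may be wider or less favourable than the primary one.
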